## Design and statistical analysis

### Quantitative data analysis

The impact of Let’s Talk on parent-clients will be examined pre, post and follow-up using analyses of variance on each of the measures outlined above. There will be a within-subjects factor (time) and a between subjects factor (intervention/control and sector of participants – adult, community and family sectors). It is intended that analyses will be undertaken on intention to treat data however deviations from protocol adherence will also be examined including any differences between participant groups on demographic characteristics.

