### Data collection

Participants will complete measures prior to randomisation and 6 weeks post the completion of the Let’s Talk intervention (including an equivalent time frame for the control group) and 6 months after the post test. Participants will have the option to complete their questionnaires by hand (and post their questionnaire), verbally over the phone or in person with one of the members of the research team.

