### Outcome measures

The primary outcome measures included the *Parental Stress Scale* [13] that measures perceived parenting stress and includes 18 items that together measure total parenting stress along with four subscales of parental rewards, parental stressors, lack of control and parental satisfaction. The *General Functioning Index* of the *McMaster Family Assessment Device* [14] measures family functioning. The General Functioning Index consists of 12 items and measures an overall score of family functioning that distinguishes between ‘effective and problematic’ family functioning. The *SF-12v2 Health Survey* [15] will be used as a measure of quality of life. The survey is a 12 item quantitative instrument that records impacts of mental and physical health on daily activities. Outcomes were measured at 6 months followup.

The secondary outcome measures were the *Parenting Self-Agency Measure* [16] that assesses the general level of confidence parents have in their ability to engage in successful parenting behaviours. The measure examines the domains of confidence, helplessness in the face of child opposition, ability to resolve parent-child conflict, and effort in parenting and persistence. The *Recovery Assessment Scale* [17] is a 22-item recovery scale commonly used in mental health services. It includes five subscales as well as a total score: Personal confidence and hope; Willingness to ask for help; Goal and success orientation; Reliance on others; and No domination by symptoms. Each of the above measures has been widely used and are well validated and exhibit strong internal consistency.

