### Participant numbers

A total of 192 parents will be recruited. Participant numbers were initially determined by a power calculation indicating a minimum *n* = 54 participants with Crit F = 2.46 (using GPOWER 3.1, assuming 3 repetitions, a small effect size, an alpha of 5% and power of 95%) to be required. The larger number of participants will account for parent dropout and to allow between group comparisons across sectors (*n* = 32 per sector per group for both intervention and control groups).

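### Treating the pre-randomisation baseline as a level of time in a repeated-measures ANOVA wastes precision at six months and, unless imputation is planned elsewhere, discards partial follow-up data

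*Protocol article*

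**What the plan says.** Under Quantitative data analysis, the protocol article states that the impact on parents "will be examined pre, post and follow-up using analyses of variance on each of the measures outlined above". It then gives the layout: "There will be a within-subjects factor (time) and a between subjects factor", the latter covering arm and sector. Data collection fixes when the first score is taken: "Participants will complete measures prior to randomisation". The pre score is thus unaffected by allocation, yet it is one of the three levels of time.

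On the analysis population, the same section says: "It is intended that analyses will be undertaken on intention to treat data". Participant numbers expects losses and answers them through recruitment: "The larger number of participants will account for parent dropout". It gives no dropout rate. The paragraph on primary outcomes under Outcome measures ends: "Outcomes were measured at 6 months followup". The article names no mixed model, no baseline adjustment and no imputation.

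**The concern.** In a trial with one baseline and two follow-ups, the baseline score carries information about each parent but none about the treatment effect. A three-level time factor spends it as a response, so the six-month arm comparison drawn from the model is a difference in change from baseline. That comparison carries the noise of both scores. Using baseline as a covariate removes only the part of it that predicts follow-up, and the result is never less precise in large samples when the variances are equal.

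The second issue is completeness. A classical ANOVA with a within-subject factor uses only rows with every wave present. If nothing else is planned, a parent who misses the post-test but returns at six months contributes nothing, and neither does one who gives the post-test and is then lost. That sits poorly with an intention-to-treat aim in a population where losses are expected. Recruiting more parents restores numbers, but it does not remove bias if loss is related to illness or arm.

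**Working it through.** **The plan's own figure.** Participant numbers gives a minimum of 54 parents "with Crit F = 2.46", for three repetitions, alpha 5%, power 95% and a small effect. For a within-between interaction, take λ = f²·N·m/(1 − r), df1 = (k − 1)(m − 1) and df2 = (N − k)(m − 1), with m = 3. With k = 3 groups, r = 0.5 and f = 0.25, this gives F(4, 102) = 2.461, minimum N = 54 and power 95.8%. With f = 0.10 and r = 0.5 the minimum N is 312 (three groups) or 260 (two arms). So 54 is not recovered when small is read as f = 0.10. That is a separate matter, and the precision comparison below does not depend on it.

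**Inputs.** From the protocol article: 192 parents, as 3 sectors × 2 groups × 32, so 96 per arm; three waves; baseline before randomisation. Assumed, because the article gives no figures: the baseline to six-month correlation r, equal variances across waves (σ² = 1), the missingness rates, and an effect of 0.4 SD. Clustering by practitioner is ignored throughout.

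**Step 1: cost of baseline as a response.** Per-parent variance of the six-month change is 2(1 − r). With baseline as covariate it is 1 − r². The ratio is (1 − r²)/[2(1 − r)] = (1 + r)/2.

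| r | change | adjusted | ratio | variance reduction |
|---|---|---|---|---|
| 0.3 | 1.40 | 0.91 | 0.65 | 35% |
| 0.5 | 1.00 | 0.75 | 0.75 | 25% |
| 0.7 | 0.60 | 0.51 | 0.85 | 15% |
| 0.8 | 0.40 | 0.36 | 0.90 | 10% |

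In terms of power, take 96 per arm, r = 0.5 and an effect of 0.4 SD. The standard error is √(2 × 1.00/96) = 0.144 for change and √(2 × 0.75/96) = 0.125 adjusted. Two-sided 5% power is 79.1% and 89.3%.

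**Step 2: cost of requiring all three waves.** If a proportion d is missing independently at each follow-up wave, complete rows number 192(1 − d)² and parents seen at six months number 192(1 − d).

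- d = 10%: 192 × 0.81 = 156 complete, 192 × 0.90 = 173 seen at six months. About 17 parents with a six-month score are lost.
- d = 20%: 192 × 0.64 = 123 complete, 192 × 0.80 = 154 seen at six months. About 31 are lost.

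If dropout is purely monotone (nobody who misses the post-test returns), everyone seen at six months has all three waves and this gap is zero. What is then discarded is the post-test score of parents lost between post-test and six months.

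**Step 3: both together, independent missingness.** A simulation of 4,000 replicates compared the baseline-adjusted analysis of all parents seen at six months with the three-wave-complete change contrast. The variance ratio was 0.68 (d = 10%) and 0.60 (d = 20%) at r = 0.5, and 0.78 and 0.66 at r = 0.7. Multiplying (1 + r)/2 by (1 − d) gives much the same: 0.75 × 0.90 = 0.675 and 0.75 × 0.80 = 0.60.

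**The case against.** Three stronger readings are tempting, and the document supports none of them.

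- **That the plan excludes parents with a missing wave and so contradicts intention to treat.** No sentence says this. Deletion of incomplete rows is how the classical method behaves, not a stated rule. ANOVA on imputed data would satisfy both statements, and missing-data handling is commonly left to an analysis plan or full protocol, neither of which is shown. The tension is therefore conditional on no such rule existing.
- **That the analysis is biased by its use of baseline.** It is not. Under randomisation the arm-by-time contrast is unbiased with baseline as a level of time. The layout is a standard one, and the loss is of precision only.
- **That the planned test misses the primary endpoint.** One sentence under Outcome measures points to six months, but the Abstract and Design both have outcomes compared at post-test and at six months. The analysis section lists factors. It neither makes an overall arm-by-time test decisive nor rules out a six-month contrast.

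Two objections to the size also stand. The gain shrinks as r rises, to 10% at r = 0.8. And the ratio is measured against a single change contrast that the protocol does not itself name, so it is not the loss for an overall test of the time profile.

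What survives is that the article does specify the method and the place of baseline within it. A different model would use the same data better under any r below 1.

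**Conclusion.** The point holds as an improvement that costs almost nothing. The specified ANOVA is a valid analysis that can be run, but it gives up precision that baseline adjustment would recover: 10% to 25% of the six-month variance for r between 0.8 and 0.5. This rests on equal variances at baseline and follow-up and on an assumed r. Because practitioners are the randomised unit and clustering was left out, the absolute powers are optimistic and the ratios could shift.

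The loss of partial data is real only if no imputation is specified elsewhere. Its size at six months runs from nothing (purely monotone dropout) to about 17 to 31 parents (10% to 20% missing independently at each follow-up wave).

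**What to change.** Replace the repeated-measures ANOVA with a linear mixed model on the post-test (t2) and six-month (t3) scores:

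- Fixed effects: baseline score, arm, time, arm × time and sector.
- Random effects: parent, and practitioner, because Recruitment makes the practitioner the unit randomised.
- Data: every parent with at least one follow-up score.

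Report the arm difference at t3 with its 95% confidence interval as the main contrast, in line with Outcome measures, and the t2 difference as secondary. This model still leaves out randomised parents with no follow-up score. Add a sensitivity analysis that covers them under missing-not-at-random assumptions, so that the intention-to-treat aim is addressed for everyone randomised.

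The cost is a change of wording and the use of standard software. No extra data, visits or participants are needed.

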**Methods:**

A two arm parallel randomised controlled trial will be used with participants, who are being treated for their mental illness in adult mental health, non-government community mental health or family welfare services. The study will involve 192 parents, who are considered by their treating practitioner to be sufficiently well to provide informed consent and participate in an intervention (Let’s Talk about Children) or control group (treatment as usual). Participant randomisation will occur at the level of the treating practitioner and will be based on whether the randomised practitioner is trained in the intervention. Outcomes are compared at pre, post intervention and six-month follow-up. Recovery, parenting and family functioning, and quality of life questionnaires will be used to measure parent wellbeing and the economic benefits of the intervention.

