Following parent completion of the first questionnaire pack, the practitioner will be randomised to either the (1) wait list control group or (2) to receive training and deliver the Let’s Talk intervention. Randomisation has been designed to occur at the practitioner level to address any potential effects of attending Let’s Talk training in the control condition. The researchers will be blind to the allocation of the practitioner, with an independent administrative officer (based at a different site to the research team) allocating practitioners to groups based on the computer generated random sequence (using SPSS). Within 1 month after being allocated, Let’s Talk practitioners will be provided with training in the intervention. The control practitioners will continue treatment as usual and will not be trained in the intervention until completion of the study. Practitioners trained in the intervention will then offer Let’s Talk to their clients. Those parent-clients who decline the intervention will continue with treatment as usual with their practitioner (and continue in the research study if they wish as a separate comparison group in the analysis). Both wait-list control and Let’s Talk trained clinicians may refer any number of eligible parent-clients to the study who indicate interest in the research.

The control group will continue to receive ‘treatment as usual’ from their non-trained (in Let’s Talk) practitioner and will be informed about (and offered) Let’s Talk as they complete the final follow up questionnaire (following the training of their treating practitioner). Treatment as usual refers to the standard treatment or model of care usually provided to clients of each of the services involved in the trial. For the purposes of the trial this will be identified as treatment as usual in adult mental health clinical services, non-government mental health community support services and family support services.

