### Randomisation and blinding

Participants will be randomly identified using a random number generator (SPSS) to intervention and control conditions. Permutation blocks of 36 will be used to ensure a minimum number of Let’s Talk and control group allocations.

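### The trial randomises practitioners, but the stated ANOVA has no practitioner term and the n = 54 power figure has no design effect

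*Protocol article*

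**What the plan says.** **Unit of randomisation.** The abstract (Methods) states: "Participant randomisation will occur at the level of the treating practitioner". The Recruitment section agrees: "Randomisation has been designed to occur at the practitioner level". It also describes an independent officer allocating practitioners, who are then either trained or wait-listed. The Limitations section likewise speaks of randomising practitioners. The Randomisation and blinding section reads differently: "Participants will be randomly identified using a random number generator (SPSS) to intervention and control conditions".

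**Cluster size.** Recruitment sets no cap. Clinicians in both arms "may refer any number of eligible parent-clients to the study".

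**Analysis.** Under Quantitative data analysis the method is analysis of variance on each measure at the three time points: "There will be a within-subjects factor (time) and a between subjects factor (intervention/control and sector of participants". No other term is listed.

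**Sample size.** Participant numbers gives a minimum of 54 with a critical F of 2.46, and lists the inputs as "using GPOWER 3.1, assuming 3 repetitions, a small effect size, an alpha of 5% and power of 95" per cent. The increase to 192 is put down to dropout and to comparisons across sectors, at 32 per sector per group.

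**The concern.** All parents of one practitioner fall in the same arm. They also share that practitioner's skill, service and fidelity to the intervention, and the Limitations section itself expects fidelity to be a difficulty. Where outcomes correlate within practitioner, the variation between parents is the wrong yardstick for an effect assigned to practitioners. The stated ANOVA uses that yardstick for every outcome, including the three primary measures.

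At stake is the validity of the arm comparison: confidence intervals that are too narrow and a false-positive rate above the nominal 5%. A larger number of parents does not cure this. The sample size was also built as if each parent were an independent observation.

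**Working it through.** **1. Reproduce the plan's figure.** From Participant numbers: 3 repetitions (T), alpha 0.05, power 0.95, critical F 2.46, n = 54. Assumed, because not stated: correlation between repetitions ρ = 0.5 and sphericity. For a group-by-time interaction with k groups and effect size f:

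- df1 = (k − 1)(T − 1), df2 = (N − k)(T − 1), λ = N·T·f²/(1 − ρ).
- With k = 3, f = 0.25, N = 54: df1 = 2 × 2 = 4, df2 = 51 × 2 = 102, λ = 54 × 3 × 0.0625/0.5 = 20.25.
- Critical F = 2.461 and power = 0.958, and 54 is the smallest N that reaches 95%.

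This matches the stated figures. No other variant tested (interaction, within-factor or between-factor test, k = 2 to 6) gave a critical F of 2.46 at N = 54. It is a calculation for independent individuals with no allowance for clustering.

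**2. Look for an allowance in 192.** 32 × 3 sectors × 2 arms = 192. The cell sizes account for the whole figure, and the reasons given are dropout and sector comparisons.

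**3. Which correlation matters.** Write the outcome of parent i of practitioner j at time t as a mean plus u(j) + v(ij) + w(jt) + e(ijt), where u is the practitioner's level, v the parent's level and w the practitioner's deviation at that time.

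- At a single time point, u and w both create within-practitioner correlation.
- In a change score, u and v cancel. What remains is w(jt) − w(j0) + e(ijt) − e(ij0), with ICC = σ²w/(σ²w + σ²e).

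So the arm-by-time test is distorted only to the extent that practitioners differ in change. A practitioner random intercept on its own models u, which has already cancelled, and so cannot correct that test.

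**4. Size.** The article gives neither the parents per practitioner (m) nor an ICC. Assumed: m from 2 to 10 and ICC from 0.01 to 0.10, where the ICC is that of the quantity tested. Formulas: DE = 1 + (m − 1)·ICC; effective N = 192/DE; the true standard error is √DE times the naive one; actual error = 2·(1 − Φ(1.96/√DE)). Power at 54 uses 54/DE in the calculation of step 1.

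| m | ICC | DE | Effective N of 192 | SE ratio | Actual error | Power at n = 54 | N needed in place of 54 |
|---|---|---|---|---|---|---|---|
| 2 | 0.01 | 1.01 | 190 | 1.005 | 5.1% | 0.956 | 55 |
| 2 | 0.05 | 1.05 | 183 | 1.025 | 5.6% | 0.948 | 57 |
| 4 | 0.05 | 1.15 | 167 | 1.072 | 6.8% | 0.924 | 63 |
| 6 | 0.05 | 1.25 | 154 | 1.118 | 8.0% | 0.897 | 68 |
| 10 | 0.05 | 1.45 | 132 | 1.204 | 10.4% | 0.838 | 79 |
| 10 | 0.10 | 1.90 | 101 | 1.378 | 15.5% | 0.702 | 103 |

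With m = 1, DE = 1 and nothing changes. The table assumes equal cluster sizes and a normal approximation. At m = 10 there would be only about 19 practitioners (192/10 = 19.2), which is why a small-sample correction is needed.

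**The case against.** **The detail may sit in a fuller protocol or analysis plan.** That would answer an omission. Here the article names the method, lists its factors and gives the basis of the sample size, and neither contains the unit it randomises.

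**Randomisation and blinding says participants are randomised.** Taken alone, that would remove the problem. But Recruitment gives the operational steps with practitioners as the unit, and explains the choice as a guard against effects of training in the control condition. The abstract and Limitations agree. The sentence is a conflict to be reconciled and does not rescue the analysis.

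**The error rate is not known.** This stands. A reader might infer that the type I error is definitely well above 5%. The documents do not support that: m and ICC are both unstated, one or two parents per practitioner is allowed, and for arm-by-time only the ICC of change counts, which may be lower than the ICC of level.

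**192 is ample for the stated target.** This also stands. A reader might infer that clustering leaves 192 underpowered. The article states no power for 192, and even at DE = 1.90 the stated target needs 54 × 1.90 = 102.6, so 103 parents before dropout. At f = 0.25, the effect size that reproduces 54, power for the two-arm interaction at 192 stays near 1. For an effect of f = 0.10 (ρ = 0.5, no dropout) it would be 0.866 with independent parents, 0.777 at m = 6 and ICC 0.05, and 0.582 at m = 10 and ICC 0.10. But whether the article's small effect means 0.10 or 0.25 is a separate question. None of this bears on the standard error, which is wrong at any N once the ICC is positive and practitioners have more than one parent.

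**Conclusion.** The stated analysis is wrong as written for the design described. Its direction of error is certain whenever practitioners contribute more than one parent and the tested quantity is positively correlated within practitioner: standard errors too small and type I error above 5%. Its size cannot be fixed from the article. Under the assumed 2 to 10 parents per practitioner and ICC of 0.01 to 0.10, it runs from trivial (DE 1.01, error 5.1%) to serious (DE 1.90, effective N 101, error 15.5%), and it is negligible if nearly all practitioners refer one parent.

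The 95% power stated for n = 54 is overstated under clustering: it falls from the reproduced 0.958 to between 0.956 and 0.702. Nothing follows from this about the power of 192, for which the article makes no claim. The change should be made before analysis, because it affects every arm comparison and costs little.

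**What to change.** 1. **Quantitative data analysis.** Replace the ANOVA with a method that respects the practitioner as the randomised unit for the arm-by-time effect. Any one of these would do, each with a small-sample correction:
   - a mixed model with random intercepts for parent and practitioner plus a practitioner-by-time random effect, and fixed effects for arm, time, arm-by-time and sector;
   - a baseline-adjusted model at each follow-up with a practitioner random intercept;
   - cluster-robust variance by practitioner.

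   A practitioner intercept alone, added to the three-time-point model, is not enough.
2. **Participant numbers.** Restate the power at n = 54 with 1 + (m − 1)·ICC over a stated range of m and ICC.
3. **Description.** Call the trial cluster-randomised in the abstract and the Design section, and reconcile Randomisation and blinding with Recruitment on the unit of allocation.

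**Cost.** Wording only. Each parent's practitioner is known, because the practitioner forwards the parent's details to the researchers, so no new data are needed. Confidence intervals become somewhat wider and the stated power less favourable.

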## Ethics and dissemination

Ethics approval for this study was obtained from Monash University Human Research Ethics Committee on January 29 2014 (approval number CF13/3300120130017) along with seven other regional health authorities. The outcomes of the trial will be disseminated at conferences and in peer reviewed journals. The general public including parents with a mental illness, their families, mental health practitioners and policy makers, will be notified of the study through public forums, government reports, policy statements, newsletters and social media.

